## 2. Abstract

### 2.1 Background

The Smart System of Disease Management (SSDM) is a series of application software developed by rheumatologists, rheumatoid arthritis (RA) patients, and Shanghai Gothic Internet Technology (Shanghai, China) for patients with chronic diseases. Preliminary studies have shown that the application of SSDM can increase the rate of RA patients with low disease activity (LDA, DAS28  $\leq$  3.2), decrease the incidence of adverse events and reduce health care costs with high satisfaction. Therefore, the rate of clinical LDA in RA patients can be improved after regularly self-assessment using SSDM.

### 2.2 Purpose

To identify the rate of patients in LDA by using SSDM at month 6.

### 2.3 Method

This is a multicenter, pragmatic randomized controlled trial. The investigators at each center will screen potentially eligible participants, explain the trial to them, check inclusion and exclusion criteria, and obtain informed consent. RA patients who sign the informed consent were evaluated for disease activity using the 28-joint disease activity score (DAS28-CRP) at baseline. According to DAS28-CRP, participants will be divided into three groups (1) Remission (REM, DAS28-CRP  $\leq$  2.6) / Low Disease Activity (LDA, DAS28-CRP 2.6 - 3.2) group; (2) Moderate Disease Activity (MDA, DAS28-CRP 3.2 - 5.1) group; (3) High Disease Activity (HDA, DAS28-CRP  $>$  5.1) group. Eligible patients will be randomly assigned at a 1:1 ratio into a SSDM group vs a conventional care control group.

[figure not shown]

**Figure 1. The randomization of this study**

Patients in the SSDM group will watch a 15-minute video that describe the key features of the SSDM to allow them to correctly use of the app. Patients will conduct self-assessment and report the results once every month for 6 months. A 6-month extension period during which subjects in the conventional care group in the initial phase will be invited to switch to SSDM group, and patients in the SSDM group will continue to use SSDM for self-management.

[figure not shown]

**Figure 2. The design of this study**

### 3. Study protocol

#### 3.1 Background

Rheumatoid arthritis (RA) is a systemic autoimmune disease characterized by persistent synovitis, systemic inflammation and autoantibodies. The prevalence of RA in China is 0.28% and there are more than 5 million patients in China. In the absence of treatment, RA can lead to functional and work disability, premature mortality. In RA patients, bone erosion and cartilage destruction may be seen within the first 2 years of the disease. DAS28-CRP  $\leq 3.2$  are the treatment target of RA.

In China, there is a significant deficit of rheumatologists. It is impossible to assess disease activity for every patient in routine practices. Meanwhile, there are no follow-up activities after these patients leaving the clinic. The window of opportunity for closely control of disease activities was easily missed.

The Smart System of Disease Management (SSDM) is a series of application software developed for patients with chronic diseases. The SSDM has iOS, Android, and Web interfaces. The functions of patient platform include evaluation, treatment, lab report, evaluation report, knowledge, and chart. The disease assessment system adopts visualization technology. Patient can complete the tender and swollen joints evaluation on the touch screen. The system automatically generates a DAS28-CRP score, and demonstrates the conditions of patients in the form of curves and charts. The self-assessment of patients can be synchronized with the physician's platform in real time. Doctors can view the data of their patients through smart phones in real time, and perform statistical analysis on the patients' data.

From 2014 to 2015, we conducted a study on the feasibility and influential factors in performing self-assessment of DAS28-CRP with SSDM in Chinese RA patients. The study confirmed that RA patients were able to perform accurate self-assessment on DAS28-CRP. The reliability of the self-assessment using SSDM reached 86%.

SSDM has been applied in rheumatology for 4 years. The preliminary cohort study results showed that the application of SSDM could improve the rate of RA patients with REM/LDA, decrease the incidence of adverse events and reduce health care costs with high satisfaction. Self-management is recommended for patients with inflammatory arthritis, patients took an active role in their disease management. In an 8-year self-management project for patients with arthritis, self-management led to long-term maintenance of self-efficacy, psychological well-being and self-management techniques. In patients with RA or psoriatic arthritis (PsA) treated with MTX, the patient's self-management could lead to significant reductions in healthcare, while maintaining clinical and psychosocial well-being. Self-assessment of disease activity in RA patients led by nurses showed more frequently changes in DMARD therapy. Smartphone as a tool for self-assessment and rehabilitation have been widely used in the rehabilitation of heart failure, asthma, diabetes and lung diseases. Therefore, smartphones are likely to become a tool for self-management in RA patients. In a survey of RA patients, 94% of RA patients believed that smartphone could have a more active role in self-management and reported it would be useful to develop a RA self-management application. Therefore, we conducted a national multi-center, randomized controlled trial to evaluate the clinical significance of self-assessment with SSDM in RA patients.

### 159 3.2 Purpose

160 The purpose of this study was to evaluate the rate of patients with DAS28-CRP  $\leq 3.2$  by using SSDM  
161 at month 6.

### 162 3.3 Study Design

163 (1) Subjects, inclusion criteria, exclusion criteria, elimination criteria, withdrawal criteria, etc.

164 **Subjects:** All patients diagnosed with RA who were treated at Peking University People's Hospital and  
165 other clinical trial centers.

#### 166 Inclusion criteria

167 1) Diagnosis of RA by investigators according to the 2010 American College of Rheumatology  
168 (ACR)/European League Against Rheumatism (EULAR) criteria

169 2)  $\geq 18$  years old

170 3) Have a smartphone

171 4) Able to evaluate disease activity by themselves

#### 172 Exclusion criteria

173 1) Not able to read and use smartphone

174 2) Not able to perform the joint examination by themselves

175 3) Patients with cognitive impairment or mental condition which make them unable to comply with the  
176 requirements of self-management

177 4) Hand deformations or any other conditions (e.g., Parkinson's disease and late-stage Alzheimer's  
178 disease) that affect data input

179 5) Do not want to accept the treatment of RA or do not plan on receiving follow-up care at the research  
180 centers

181 6) Already a user of SSDM

182 Elimination criteria: Patients with incomplete clinical data.

183 Withdrawal criteria: Patients who request to withdraw from the clinical trial.

184 (2) Randomization of subjects, whether to set up a control group

#### 185 1) Randomization

186 Following the evaluation by rheumatologists, eligible participants will be randomized at a 1:1 ratio to a  
187 SSDM group vs a conventional care control group. The randomization sequence was generated with an  
188 interactive web response system (BioVoicer Technology Co. Ltd, Beijing, China) using a block design  
189 (block sizes of 4). The randomization was stratified based on the DAS28-CRP score at the baseline ( $\leq$   
190 3.2, 3.2 - 5.1, or  $> 5.1$ ). Concealment was conducted centrally using an interactive web response  
191 system.

#### 192 2) Intervention

193 ① SSDM intervention group: Upon the first use of the system, the following information must be  
194 entered with the help of a research staff: full name, sex, date of birth, date of initial diagnosis,  
195 comorbidities, education level, occupation, family income, annual medical expenses and DAS28-CRP  
196 at each research site. Other information that entered included: 1) lab results (e.g., routine blood test,  
197 liver and kidney function, erythrocyte sedimentation rate, CRP), submitted as photographs and  
198 automatically processed to extract key information via Optical Character Recognition technology; 2)  
199 medications, for RA as well as co-morbid conditions; and 3) perceived adverse reactions (a total of 33  
200 types of symptoms).

201 Patients randomized to the SSDM group watch a 15-minute video that described the key features of  
202 SSDM to allow correct use of the app. After learning, the patients will do the self-assessment all by  
203 themselves using SSDM. If there is inconsistency between patient and physician, the physician will  
204 correct it and then the patient will do it again. At last, the use of SSDM by patients and self-assessment

205 of DAS28-CRP were confirmed by physicians.

206 ② Conventional care control group: Patients randomized to the control group will receive  
207 conventional care, and should come back for office visits at month 6 and month 12. The information of  
208 baseline characteristics will also be collected.

209 All the primary and secondary endpoint will be assessed by rheumatologists.

### 210 (3) Intervention measures

211 Duration of the Study: 12 Months

### 212 (4) Follow-up Plan

| Period                       | Screening | Follow-up Period |    |    |     |     |     |     |     |     |     |     |     |
|------------------------------|-----------|------------------|----|----|-----|-----|-----|-----|-----|-----|-----|-----|-----|
| Time (Month)                 | 0         | 1                | 2  | 3  | 4   | 5   | 6   | 7   | 8   | 9   | 10  | 11  | 12  |
| Follow-up(day)               | 0         | 30               | 60 | 90 | 120 | 150 | 180 | 210 | 240 | 270 | 300 | 330 | 360 |
| ICF signing                  | ×         |                  |    |    |     |     |     |     |     |     |     |     |     |
| Inclusion/exclusion criteria | ×         |                  |    |    |     |     |     |     |     |     |     |     |     |
| Demographic data             | ×         |                  |    |    |     |     |     |     |     |     |     |     |     |
| DAS28-CRP                    | ×         | ×                | ×  | ×  | ×   | ×   | ×   | ×   | ×   | ×   | ×   | ×   | ×   |
| CDAI                         | ×         | ×                | ×  | ×  | ×   | ×   | ×   | ×   | ×   | ×   | ×   | ×   | ×   |
| SDAI                         | ×         | ×                | ×  | ×  | ×   | ×   | ×   | ×   | ×   | ×   | ×   | ×   | ×   |
| HAQ                          | ×         | ×                | ×  | ×  | ×   | ×   | ×   | ×   | ×   | ×   | ×   | ×   | ×   |
| SF-36                        | ×         | ×                | ×  | ×  | ×   | ×   | ×   | ×   | ×   | ×   | ×   | ×   | ×   |
| HADS                         | ×         | ×                | ×  | ×  | ×   | ×   | ×   | ×   | ×   | ×   | ×   | ×   | ×   |
| Morning stiffness            | ×         | ×                | ×  | ×  | ×   | ×   | ×   | ×   | ×   | ×   | ×   | ×   | ×   |
| Medication                   | ×         | ×                | ×  | ×  | ×   | ×   | ×   | ×   | ×   | ×   | ×   | ×   | ×   |

213 (5) Selection and confirmation of primary measurement indicators or outcome indicators, secondary  
214 observation endpoints

### 215 1) The Primary Endpoint

216 The primary endpoint is the rate of DAS28-CRP  $\leq 3.2$  at month 6, as assessed by rheumatologists

### 217 2) The Secondary Endpoint

218 ① The rate of DAS28-CRP  $\leq 3.2$  between the two groups at month 12, assessed by rheumatologists.

219 ② The RA flare rate between the two groups at month 6 and 12.

220 ③ The proportion of patients with moderate-to-good EULAR response between the two groups at  
221 month 6 and 12.

222 ④ ACR/EULAR Boolean remission rate between the two groups at month 6 and 12.

223 ⑤ The HADS between the two groups at month 6 and 12.

224 ⑥ The SF-36 between the two groups at month 6 and 12.

225 ⑦ Clinical disease activity index (CDAI) between the two groups at month 6 and 12.

226 ⑧ The numbers of tender joint counts and swollen joint counts between the two groups at month 6 and  
227 12.

⑨ The effect of active intervention by doctors between the two groups at month 6 and 12.

⑩ The number and rate of adverse events, either reported by the rheumatologists or resulting from an alert in the SSDM.

#### (6) Sample Size

Sample size calculation 1) 6-month disease control rate of 44.3% in the control group and 52% in the SSDM group; 2) 2-sided  $\alpha$  at 0.05 and power at 90%; 3) 20% attrition rate. The calculation yielded a total of 2200 patients. And 2204 were the minimum sample size created by the Random Number Generator.

(7) The enrollment period, whether to design an interim analysis

The enrollment is expected to be half a year.

### 3.4 Previous results

(1) We verified the feasibility and influential factors in performing self-evaluation on DAS28-CRP with SSDM by RA patients from December 14, 2014 to February 2, 2015. This study included two phases. In the first phase, 55 cases were enrolled. The intra-class correlation coefficient (ICC) of tender joint counts (TJCs) and DAS28-CRP scores were 0.93 and 0.94, but the ICC of swollen joint counts (SJC) was 0.68. The analysis showed that the duration of disease was the only associate factor with significant difference ( $P < .05$ ). In the second phase, the education courses were more emphasized in identification of swollen joints. As a result, the ICCs of SJC, TJCs and DAS28-CRP were improved to 0.93, 0.93 and 0.92, respectively. RA patients could master SSDM and perform accurate self-evaluation on DAS28-CRP and HAQ.

(2) Another study evaluated the patterns of T2T and related influential factors among RA patients after applying SSDM in real world. From June 2014 to June 2017, 1,232 RA patients from 145 hospitals across China were followed up for more than 6 months through SSDM. The rate of patients in REM/LDA was 40% (491/1,232) at baseline, and improved significantly to 64% (793/1,232) after 6 month follow up. Among patients in REM/LDA at baseline, 75% (369/491) maintained LDA, 25% (122/491) relapsed. Compared with relapsers, patients with LDA performed more self-evaluation (5.78 vs 4.73,  $P = .017$ ), higher rate on DMARDs (69% vs 59%), lower rate on NSAIDs (4% vs 13%,  $P < .01$ ) or glucocorticoid (3% vs 8%,  $P < .01$ ). Among patients failed to reach REM/LDA at baseline, 57% (424/741) achieved REM/LDA after 6 months. Comparing with 6 month failure (317/741), new REM/LDA achiever got shorter morning stiffness time ( $16.77 \pm 27.12$  vs  $27.03 \pm 33.76$  minutes,  $P < .001$ ), lower HAQ score ( $2.17 \pm 3.36$  vs  $3.36 \pm 4.05$ ,  $P < .001$ ) at baseline, performed more self-evaluation (6.56 vs 5.35,  $P = .007$ ). However, even in patients of 6 month failure, the morning stiffness time and HAQ score improved significantly in final follow up comparing with those at baseline ( $16.59 \pm 28.76$  vs  $27.03 \pm 33.76$ ,  $P < .001$ ;  $2.77 \pm 3.52$  vs  $3.36 \pm 4.05$ ,  $P < .001$ ).

### 3.5 Clinical Study Site and Data Management

The study does not involve sample collection, storage sites and laboratory research sites.

The data in this study are divided into electronic data and paper data. The paper data should be archived and stored in the order of labeling for inspection. Electronic data files include databases, inspection procedures, analysis procedures, analysis results, codebooks and instruction documents, etc., which should be stored in categories. Multiple backups of electronic data should be stored on different disks or recording media to prevent damage. All original data should be kept within the required time limit.

Electronic data is stored on the Alibaba Cloud. The security of the data is protected by the corresponding laws and regulations.

### 3.6 Statistical analysis

All endpoints will be analyzed in a modified intent-to-treat (ITT) population that excluded patients with incorrect diagnosis (autoimmune diseases other than RA) upon enrolment. Sensitivity analysis will be performed to assess the robustness of the primary analysis using multiple imputation, last observation carried forward imputation, and the worst case scenario imputation. The primary endpoint will also be analysed using the per-protocol (PP) analysis, inverse probability of censoring weighted (IPCW) method. Continuous variables are defined as mean (standard deviation, SD) or median (inter-quartile range, IQR) and will be compared between the two groups using the Student's t-test or Wilcoxon

rank-sum test. Categorical variables are defined as frequency or percentage and compared between the two groups using  $\chi^2$  or Wilcoxon rank sum test, as appropriate. The trend of changes in DAS28-CRP and EULAR responses was calculated from baseline to month 6. Preplanned subgroup analyses will be conducted based on disease activity at baseline. Other subgroup analyses were post hoc. Statistical significance are set at 2-sided  $P < .05$ . All data analyses are conducted using the using the SAS and R.

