#### (3) Per-Protocol (PP) population

Patients who complete the treatment and follow-up and outcome information is available at each time point will be included in the PP population. The per protocol analysis includes only adherent participants (adherence rate > 50%). The number of patients in the PP analysis at month 6 was 968 in SSDM group and 886 in control group. The number of patients in the PP analysis at month 12 was 949 in SSDM group and 860 in control group.

Logistic regression, adjusting for baseline stratifications will be used to analyze the binary efficacy variables. The primary and second endpoints will be performed on both the mITT population and the PP population. The primary endpoint will also be analyzed using the worst-case scenario imputation, and the inverse probability of censoring weighted (IPCW) method.

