#### 6.9 Missing Data

The missing mechanism analysis will be performed. The missing data will be imputed using multiple imputation.

(1) Multiple-imputation method will be used to handle missing data under the missing at random assumptions.

(2) Five imputed data sets will be generated for the missing data. The missing values will be imputed using fully conditional specification (FCS) with the Multivariate Imputation by Chained Equations (mice) package (version 3.14.0) for R (version 4.2.1), and we will predictive mean matching (PMM) for the imputation of continuous variables. The baseline characteristics are included as auxiliary variables. Observed values and distributions of imputed data will be compared.

(3) The primary and secondary endpoints of each imputed datasets will be analyzed separately. And combined inferences from five imputed data sets are based on Rubin's rules.

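### The documents do not fix one rule for missing month-6 outcomes, and the LOCF and worst-case checks are too loosely defined to show robustness if loss differs by arm

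*Combined protocol and SAP*

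**What the plan says.** Five places bear on a missing month-6 outcome.

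- **Protocol 3.3, after the exclusion criteria:** "Elimination criteria: Patients with incomplete clinical data". The stage and analysis set are not stated. SAP section 4 repeats the eligibility and withdrawal criteria but not this one.
- **SAP 6.4 (1) and (2):** ITT is everyone randomised and mITT is everyone eligible and randomised. Neither requires complete data. Protocol 3.6 removes only wrong diagnoses from its modified ITT set.
- **Protocol 3.6:** the primary result is checked "using multiple imputation, last observation carried forward imputation, and the worst case scenario imputation". Here MI is a sensitivity analysis. Per-protocol (PP) and IPCW analyses are also listed.
- **SAP 6.9:** missing data are imputed by MI under missing at random (MAR), and the primary and secondary endpoints are analysed in each imputed set. "Five imputed data sets will be generated for the missing data".
- **SAP 6.4 (3):** worst case and IPCW are added for the primary endpoint. LOCF does not appear in the SAP.

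The same SAP section reports PP numbers: "The number of patients in the PP analysis at month 6 was 968 in SSDM group and 886 in control group". At month 12 they are 949 and 860. PP membership needs outcome data at each time point and adherence above 50%.

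On assessment timing, SSDM: "Patients will conduct self-assessment and report the results once every month for 6 months" (Protocol 2.3). Control patients "should come back for office visits at month 6 and month 12" (Protocol 3.3, Intervention). The follow-up table in Protocol 3.3 (4) shows monthly DAS28-CRP without separating the arms. The primary endpoint is rheumatologist-assessed (Protocol 3.3 (5)).

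**The concern.** Elimination, MI as a check and MI as the method give different primary estimates from the same data, so the estimate is not uniquely specified.

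The PP counts also suggest that more control patients were excluded. Attrition is planned at 20% overall with no split by arm, and neither document discusses unequal loss. If loss is unequal, two of the named checks may lean towards SSDM. Worst case read as failure in both arms penalises the arm with more missing outcomes. LOCF may carry baseline for a control patient but a later self-assessment for an SSDM patient. A check that can err towards the hypothesis cannot confirm it.

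**Working it through.** **Inputs.** Protocol 3.3 (6) plans on a "6-month disease control rate of 44.3% in the control group and 52% in the SSDM group", a 7.7 pp effect, with two-sided alpha 0.05, 90% power, 20% attrition and 2,200 patients (2,204 minimum). PP counts come from SAP 6.4 (3). The 40% and 64% response rates at baseline and six months come from the earlier SSDM cohort in Protocol 3.4, which had no control group. Using them here is an assumption.

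**1. The plan's sample size reproduces.** (1.960 + 1.282)² × (0.443×0.557 + 0.52×0.48) / 0.077² = 879.6, so 880 per arm. 880/0.8 = 1,100, or 2,200 in total. (Pooled variance gives 883 per arm and 2,208.)

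**2. Exclusion gap.** Randomised counts per arm are not given. Assume 2,204 split 1:1, or 1,102 per arm.

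| | SSDM excluded | Control excluded | Gap |
|---|---|---|---|
| Month 6 | 134/1,102 = 12.2% | 216/1,102 = 19.6% | 82/1,102 = 7.4 pp |
| Month 12 | 153/1,102 = 13.9% | 242/1,102 = 22.0% | 89/1,102 = 8.1 pp |

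For equal arms of 1,000 to 1,200 the month-6 gap is 8.2 to 6.8 pp. For arms of 1,120 SSDM and 1,084 control it is 4.7 pp; with those sizes reversed, 10.2 pp.

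Steps 3 to 5 treat every PP exclusion as a missing outcome. At this arm size that is the most that can be missing in each arm. It is not a bound on the gap between arms.

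**3. Worst case.** If missing means failure in both arms and the true rate is p in both, the difference is p × (968 − 886)/1,102 = 0.0744p. The last column uses a normal-approximation two-proportion test without centre adjustment.

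| p | SSDM | Control | Difference | Chance of a significant SSDM benefit (nominal 2.5%) |
|---|---|---|---|---|
| 44.3% | 38.9% | 35.6% | +3.3 pp | 36% |
| 52% | 45.7% | 41.8% | +3.9 pp | 45% |
| 64% | 56.2% | 51.5% | +4.8 pp | 61% |

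At the planned rates the 7.7 pp effect becomes 0.52×0.8784 − 0.443×0.8040 = 10.1 pp. Set against SSDM instead (SSDM missing = failure, control missing = success), it becomes 0.4568 − (0.3562 + 0.1960) = −9.5 pp. The result turns on a definition that the documents do not give.

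**4. LOCF, no true effect, 40% baseline rate.**

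- Baseline carried in both arms: 0.0744 × (p − 0.40) = +0.3, +0.9 and +1.8 pp at p = 44.3%, 52% and 64%.
- Baseline carried in control, and a late self-assessment already at rate p carried in SSDM: 0.1960 × (p − 0.40) = +0.8, +2.4 and +4.7 pp.

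**5. Elimination, no true effect, p = 44.3%.** If patients with missing data respond at rate m in both arms, the observed rate is (p − d×m)/(1 − d), where d is the missing share.

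- m = 30%: 46.3% v 47.8%, −1.5 pp (against SSDM).
- m = 44.3%: 0.
- m = 60%: 42.1% v 40.5%, +1.7 pp.

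**6. Number of imputations.** Take the fraction of missing information as 0.16 (overall exclusion is 350/2,204 = 15.9%) and a standard error of about 2.2 pp. Monte Carlo SD is √(0.16/m) × 2.2, where m is now the number of imputations: about 0.4 pp with 5 and 0.1 pp with 50. It has no direction.

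**The case against.** The strongest reply is that the main method is sound. SAP 6.9 applies MI to the primary and secondary endpoints, and if MAR holds, unequal loss alone does not bias it. IPCW is planned too, and the SAP does not carry LOCF forward. That stands, so the trial's primary result is not shown to be biased. But Protocol 3.6 still calls MI a sensitivity analysis, and no planned analysis varies departures from MAR by arm.

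A reader might infer from 968 and 886 that control lost at least 7 pp more outcomes. The documents do not support that. The counts mix missing outcomes with an adherence filter that is not defined for control, and the denominator is assumed. If the filter removed mainly SSDM patients whose outcome was known, the missing-outcome gap is larger. If control patients with a month-6 outcome failed PP for another reason, it is smaller.

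A reader might also take LOCF to be asymmetric by design. That is open. Because the endpoint is rheumatologist-assessed, self-assessments may not be eligible to carry, and baseline would then be carried in both arms. If the monthly follow-up table applies to control as well, control has more than baseline to carry. At the planned control rate of 44.3% the bias is only +0.3 to +0.8 pp.

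The elimination line need not make the analysis complete-case, since its scope is unstated and the SAP omits it.

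**Conclusion.** The concern holds in a limited form. The conflict between elimination, an mITT set with no completeness requirement, MI as a check and MI as the method needs no assumption. The month-6 PP counts suggest about 7.4 pp more exclusion in control at 1,102 per arm.

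The bias figures are conditional on every PP exclusion being a missing outcome. Worst case gives +3.3 to +4.8 pp only if it means failure in both arms. LOCF gives +0.3 to +4.7 pp, and the top of that range needs a 64% true rate and late self-assessments carried in SSDM. Against a planned effect of 7.7 pp, this is enough that these checks cannot on their own show a positive result to be robust.

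It would be tempting to conclude that the plan builds in a spurious SSDM advantage, or that the trial's false-positive rate is 36% to 61%. Neither follows. Those rates describe one reading of one sensitivity analysis, another reading runs strongly against SSDM, and elimination can go either way.

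**What to change.** - Remove the elimination criterion, or state that it does not apply to ITT or mITT.
- Name MI in the mITT population as the primary handling in both documents.
- Drop LOCF, or restrict it to rheumatologist assessments scheduled in both arms. Reconcile the follow-up table with the control-arm visit text.
- Replace the undefined worst case with MI plus a delta or tipping-point grid, with the two arms shifted separately and shifts against SSDM included.
- Include arm, baseline stratum and centre in the imputation model. Use month-12 values only with arm-specific imputation, because control patients move to SSDM after month 6.
- Report randomised, mITT and missing-outcome counts by arm.
- Optionally raise the number of imputations, for example to 50. This reduces only Monte Carlo noise.

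The cost is revised wording and some programming, with no new data. The downside is that the robustness results may look less favourable.
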